## Abstract

**Background:**

Rheumatoid arthritis (RA) disease activity during disease-modifying antirheumatic drug (DMARD) tapering is commonly monitored using in-person clinical assessment and the 28-joint Disease Activity Score with C-reactive protein (DAS28-CRP). Although effective, this approach is resource intensive and may be inconvenient for patients. Remote monitoring with patient-reported outcomes and wearable sensors may enable earlier flare detection and support safer, more personalized tapering pathways. Prior pilot work suggests that accelerometry-derived physical activity, mobility, and sleep metrics correlate with RA disease activity and are acceptable to patients.

**Objective:**

This protocol aims to evaluate the feasibility and diagnostic accuracy of remote monitoring for detecting RA flare during DMARD tapering. The study will (1) continuously measure physical activity and quality metrics using wrist-worn accelerometers, (2) collect weekly Rheumatoid Arthritis Flare Questionnaire (RA-FQ) scores, (3) develop and evaluate dynamic risk prediction models using longitudinal accelerometry-derived measurements to estimate the risk of clinically confirmed flare, (4) retrospectively assess prediction accuracy against patient-reported flare, and (5) develop and evaluate a combined dynamic prediction model incorporating longitudinal accelerometry-derived measurements and total RA-FQ scores to assess whether the addition of the RA-FQ improves the prediction of clinically confirmed flare.

**Methods:**

This prospective, single-center observational cohort study is embedded within the Rheumatoid Arthritis DMARD Tapering (ROADMAP) clinic at Freeman Hospital, Newcastle upon Tyne, United Kingdom. Adults with clinician-confirmed RA in remission who are undergoing or are about to begin DMARD tapering will be recruited, with a target sample of 100 participants. Participants will be followed for 12 months, with clinical assessments aligned with routine ROADMAP visits at baseline and approximately months 3, 6, 9, and 12 together with ad hoc visits for suspected flare. Continuous wrist-worn accelerometry and weekly RA-FQ responses will be collected throughout follow-up. Clinical assessments will include tender and swollen joint counts, patient and physician visual analog scales, C-reactive protein, the DAS28-CRP, and Health Assessment Questionnaire Disability Index scores. The primary outcome is time to first clinically confirmed flare, defined as DAS28-CRP≥2.4 and/or at least 1 swollen joint attributable to inflammatory RA activity. Dynamic risk prediction methods, such as landmarking models, will use longitudinal accelerometry-derived physical activity, mobility, gait, and sleep measures to estimate flare risk over prespecified prediction horizons. Model performance will be assessed using time-dependent discrimination, calibration, predictive values, and lead time before clinically confirmed flare.

**Results:**

The first participant was recruited in October 2025. As of July 2026, 16 participants had been recruited. This protocol reports the study design and planned analyses; outcome analyses will be conducted after recruitment and 12-month follow-up are complete.

**Conclusions:**

This study will provide pilot evidence on the feasibility and accuracy of multimodal remote monitoring for RA flare detection during DMARD tapering in routine care. Findings will inform model refinement, external validation, and future larger multicenter studies evaluating clinical utility and service impact.

## Introduction

Rheumatoid arthritis (RA) is a common disease affecting approximately 1 in 100 adults in the United Kingdom [1] and is characterized by joint pain and swelling and general features such as fatigue [2]. Patients with RA are prescribed disease-modifying antirheumatic drugs (DMARDs) in order to prevent joint damage and improve symptoms [3]. With modern treat-to-target DMARD regimens, approximately two-thirds of patients newly diagnosed with RA can now achieve disease remission. Once remission is achieved, international clinical guidelines now endorse the gradual reduction (tapering) of DMARDs to reduce the risk of drug side effects and toxicity, reduce medication burden for patients, and reduce drug prescription costs.

The Rheumatoid Arthritis DMARD Tapering (ROADMAP) service was established in early 2023 at Newcastle Hospitals to support a consistent, standardized approach to DMARD tapering for patients with RA seen in rheumatology outpatient clinics [4]. Patients may enter the service while receiving either a full therapeutic dose or a previously reduced but stable dose; therefore, enrollment in this service is not restricted to patients beginning their first tapering step. Tapering is individualized according to DMARD class, current dose, duration of remission, previous tapering history, and clinical judgment. Dose reductions are generally introduced stepwise at approximately 3-month intervals rather than through an immediate reduction (eg, to 50% of the original dose) [4]. At each visit, the current dose, proportion of the reference therapeutic dose, date and magnitude of the most recent reduction, and planned next tapering step are recorded. If flare occurs, treatment is returned to the previously effective dose, with short-term bridging glucocorticoids used when clinically indicated.

In routine clinical care, RA disease activity is commonly evaluated using a composite measure based on tender and swollen joint counts, an inflammatory biomarker (C-reactive protein [CRP] or erythrocyte sedimentation rate [ESR]), and a patient-rated visual analog scale, which together generate the 28-joint Disease Activity Score (DAS28) [5-7]. Because this assessment typically requires in-person hospital visits, ongoing monitoring can be resource intensive and costly [8,9]. In addition, patients in sustained remission are often reviewed infrequently (typically annually), meaning that scheduling 3-monthly outpatient appointments during DMARD tapering can be inconvenient for patients and may represent an inefficient use of clinician time and hospital resources.

Compared with DAS28-based monitoring, several patient-reported outcome measures (PROMs) have been developed to identify RA flare using self-completed questionnaires that capture multiple dimensions of disease activity, including fatigue, pain, mood, and physical function [10]. One widely evaluated instrument is the Rheumatoid Arthritis Flare Questionnaire (RA-FQ), which has been endorsed by the international OMERACT consortium for this purpose [11]. PROMs can be completed remotely without hospital attendance and can capture subjective aspects of disease impact that are not directly represented within the DAS28 framework. In parallel, advances in accelerometry have enabled wearable devices that remotely measure and quantify physical activity and gait characteristics [12]. In prior work, wrist-worn and lower back–worn accelerometers were used to derive activity and gait metrics in 11 patients with active RA who were newly initiating DMARD therapy [13]. These pilot findings indicated strong correlations between accelerometry-derived outcomes and clinical indicators of disease activity, particularly inflammatory biomarkers (CRP and ESR) and tender joint count. Patient feedback also suggested high acceptability of the devices, with a preference for the wrist-worn placement [14]. To this end, the main objective of this study is to demonstrate the feasibility and accuracy of accelerometry monitoring for the detection of RA flare during DMARD tapering. Primary and secondary subobjectives of the study are presented in Textbox 1.

Textbox 1.Primary and secondary objectives of the study.
**Primary subobjectives**
Predict clinically confirmed flare risk using dynamic risk prediction methods based on longitudinal accelerometry-derived measurementsAssess retrospectively the accuracy of the dynamic risk prediction models for flare prediction vs patient-reported flare
**Secondary subobjectives**
Assess the usability and acceptability of continuous accelerometry monitoring using patient feedback questionnairesAssess retrospectively the accuracy of Rheumatoid Arthritis Flare Questionnaire (RA-FQ) flare prediction vs clinically confirmed flareDevelop and evaluate a combined dynamic prediction model incorporating longitudinal accelerometry-derived measurements and the RA-FQ total score to predict clinically confirmed flare and compare its performance with that of the accelerometry-only model

## Methods

### Study Design

This prospective, single-center observational cohort study is embedded within the ROADMAP DMARD tapering clinic at Freeman Hospital, Newcastle upon Tyne, United Kingdom (Multimedia Appendix 1). Adults with clinician-confirmed RA in remission who are undergoing or are about to begin DMARD tapering will be followed for 9 months. Continuous wrist-worn accelerometry and weekly RA-FQ responses will be collected throughout follow-up, with clinical assessments aligned with routine ROADMAP visits at baseline and approximately months 3, 6, 9, and 12 together with ad hoc visits for suspected flare.

### Ethical Considerations

Patients will be required to attend face-to-face hospital visits on a maximum of 3 occasions during study follow-up. To avoid additional study visits beyond standard clinical care, we have aligned the study visits with the clinic visit schedule of the ROADMAP clinic, thus avoiding additional trips to the hospital for participants [13,14]. Under the currently approved protocol, participants may be followed for up to 6 months. An amendment has been submitted to the Health and Care Research Wales Research Ethics Committee (REC) to extend the maximum follow-up period by an additional 6 months, from 6 to 12 months. The amendment is currently under review by the same REC. The extended follow-up procedures will not begin until a favorable ethical opinion and all required sponsor and site approvals have been obtained.

The study was approved by the Health and Care Research Wales REC (reference 25/WA/0043). All participants will provide written informed consent before enrollment, and additional consent will be obtained for the extended follow-up where required. The study will be conducted in accordance with the Declaration of Helsinki, and it was prospectively registered with ISRCTN (ISRCTN14472047) before the recruitment of the first participant. The completion of the weekly RA-FQ through the REDCap portal requires access to a computer or mobile device, internet access, and sufficient digital literacy. To reduce exclusion related to digital access, participants unable to use REDCap will be provided with paper RA-FQs.

Tapering of DMARD therapy is associated with a risk of arthritis flare. In our previous research studies and based on outcomes to-date from the ROADMAP clinic, the risk of flare is approximately 50% [15]. Importantly, the patients in this study taper their DMARDs as part of routine clinical care within the ROADMAP clinical service, which lies outside the scope of this project protocol. Patients are informed of this risk, which is discussed in detail during their initial ROADMAP clinical consultation prior to participation in this study and thus does not form part of the ethical considerations of this study protocol.

### Target Recruitment Sample Size

This is explicitly a development project phase, and as such the analysis is intended to produce pilot data to support and inform the design of a future larger definitive trial of remote monitoring in DMARD tapering. To determine the required sample size for the current study, our primary focus lies in testing whether the area under the curve (AUC) derived from the risk prediction model is significantly greater than a cut-point of 0.6. Assuming a true AUC of 0.8 and flare rate of 50%, we will be able to reject the null hypothesis (H0: AUC ≤0.6) with 90% power and a 2-sided type I error rate of 0.025 with a target recruitment size of 100 patients.

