### Primary Analyses

The primary outcome is the time from study enrollment to the first clinically confirmed RA flare, defined as a DAS28-CRP of 2.4 or above.

The primary objective of the study is to predict clinically confirmed flare risk using dynamic risk prediction methods based on daily accelerometry data including both the quality metrics and the physical activity measures. In addition, we would like to retrospectively assess the accuracy of the model vs patient-reported flare.

We will use landmarking models to develop a dynamic risk prediction approach for arthritis flare. Landmarking is a time-updated survival modeling framework that generates risk predictions at predefined time points (landmark times) using information available up to each time point. Predictions are then made over specified future time horizons.

The approach consists of two components:

A longitudinal submodel, which summarizes repeated accelerometry-derived measurements over timeA time-to-event submodel, which estimates the risk of flare from each landmark time

At each landmark time, the longitudinal submodel is used to extract summary measures of the accelerometry data up to that time, and these summaries are then included as predictors in the time-to-event model to estimate the future risk of flare.

The event of interest is the first clinically confirmed arthritis flare. Participants who do not experience a clinically confirmed flare will be censored at the end of their individual follow-up period or at earlier withdrawal.

For the time-to-event component, we will fit both Cox proportional hazards models and random survival forests (RSFs) to assess potential improvements in predictive performance and capture potential nonlinear relationships and interactions. We also consider including variables such as age, sex, Clinical Frailty Score, and anticitrullinated protein antibodies (ACPAs) antibody status (either positive/negative or the actual titer) as fixed effects or variables in both longitudinal and time-to-event submodels as they are clinically important.

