The model will be generated at weekly landmark times throughout follow-up. At each landmark, the model will use all accelerometry data collected up to that time to estimate the probability of clinician-defined flare occurring within the subsequent 14 days. Weekly updating allows risk estimates to be refreshed throughout DMARD tapering and provides clinically actionable information to support decisions regarding continuation or modification of tapering.

We will also evaluate the accuracy of the model’s flare predictions for each prediction time window against patient-reported flares derived from the RA-FQ, based on responses to the yes or no question about current flare status. Patient-reported flare status will serve as the reference standard. Model-predicted flares will be compared against patient reports to calculate sensitivity, specificity, and agreement (Cohen κ). It helps to assess how well the model’s predictions align with patient perception.

Sensitivity: proportion of patient-reported flares that are correctly predicted by the model (true-positive rate); higher values, close to 100%, are desirable.Specificity: proportion of patient-reported nonflares that are correctly identified as no flare by the model (true-negative rate); higher values, close to 100%, are desirable.Agreement: measured using Cohen κ to quantify concordance between model-predicted and patient-reported flares; higher values, close to 1, indicate stronger agreement beyond chance.

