### Future Directions

The most important next step after this study will be external validation of the flare prediction model in larger and more diverse cohorts, ideally across multiple sites and health systems. Future work should also assess whether integrating wearable-based flare alerts into routine care improves patient outcomes, clinician workload, and service efficiency compared with standard tapering follow-up alone. In addition, model refinement may benefit from combining accelerometry and RA-FQ data directly in a unified prediction framework, as these data sources likely capture complementary aspects of flare onset and patient experience.

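### The 90% power is worked out for a fixed marker in a sample with 50% flares; it is not established for the AUC of a 14-day weekly landmark model developed in the same patients

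*Protocol article*

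**What the plan says.** Target Recruitment Sample Size gives the primary focus as "testing whether the area under the curve (AUC) derived from the risk prediction model is significantly greater than a cut-point of 0.6". The justification reads "Assuming a true AUC of 0.8 and flare rate of 50%, we will be able to reject the null hypothesis", "with 90% power and a 2-sided type I error rate of 0.025 with a target recruitment size of 100 patients". These inputs describe one flare/no-flare classification with 50 patients on each side.

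Primary Analyses plans a landmark time-to-event model, generated weekly, that will "estimate the probability of clinician-defined flare occurring within the subsequent 14 days". For the time-to-event part, "we will fit both Cox proportional hazards models and random survival forests (RSFs"), with accelerometry summaries as predictors and clinical variables under consideration. The Abstract lists time-dependent discrimination among the performance measures.

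No section ties the tested AUC to a landmark, to the 14-day horizon or to a value pooled over landmarks. On validation, Future Directions says "The most important next step after this study will be external validation of the flare prediction model". The article does not say whether performance within this study is apparent or internally validated.

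Follow-up is 12 months in the Abstract, 9 months in Study Design and, as currently approved, up to 6 months in Ethical Considerations. The flare risk of about 50% in Ethical Considerations carries no time span.

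**The concern.** The prevalence behind the power statement is a whole-follow-up figure, while the prediction target is a two-week window. The precision of an AUC is governed mainly by the smaller group, so replacing 50 flares with a handful changes the power completely. In addition, a one-sample test against 0.6 treats the marker as given. Here the score is estimated from the same 100 patients, with several families of accelerometry features and two model classes. An uncorrected AUC from such a model is biased upward.

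This is the only test the article powers, and its result is meant to inform a larger definitive trial. A reader cannot tell whether the stated power and error rate belong to the quantity that will be reported.

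**Working it through.** **Inputs from the article.** AUC 0.6 (null) and 0.8 (alternative); 50% flares; N=100; 2-sided 0.025, so z=2.241 and 0.0125 in the upper tail; weekly landmarks; 14-day horizon.

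**Assumption.** 50 first flares among 100 patients at constant hazard over follow-up of T weeks. The article gives no time course.

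**Formula (Hanley-McNeil).** With m flare and n flare-free observations, Q1=A/(2−A) and Q2=2A²/(1+A):

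Var(A) = [A(1−A) + (m−1)(Q1−A²) + (n−1)(Q2−A²)]/(mn)

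Power = Φ((0.2 − 2.241·SE0)/SE1), where SE0 is at 0.6 and SE1 at 0.8.

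**1. The plan's own design, m=n=50.** SE0=0.0566 and SE1=0.0445. Power = Φ((0.2−0.1269)/0.0445) = Φ(1.64) = 95%. The binormal variance gives 94%. The N needed for 90% is 86 and 90 respectively. So 100 is slightly conservative for a fixed marker.

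**2. Flares in one 14-day window, and power there.** Hazard = ln2/T. The first window holds 100(1−e^(−2·ln2/T)) flares. The last holds that number times the share still flare-free at T−2 weeks.

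| Follow-up | Flares, first window | Power | Flares, last window | Power |
|---|---|---|---|---|
| 52 weeks | 2.6 | 9% | 1.4 | 5% |
| 36 weeks | 3.8 | 14% | 2.0 | 7% |
| 24 weeks | 5.6 | 21% | 3.0 | 10% |
| 12 weeks (main period only) | 10.9 | 43% | 6.1 | 22% |

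Example, 52 weeks, first window: SE0=0.188 and SE1=0.166, so Φ((0.2−0.421)/0.166) = Φ(−1.33) = 9%.

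The normal approximation is rough at such counts. A simulation with the test size held at 0.0125 gives 12% with 2 flares, 16% with 3 and 42% with 8. Reaching 90% in one window takes about 35 flares among 100.

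**3. AUC pooled over landmarks.** With many flare-free windows, precision depends on the number of flares:

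- 50 flares: SE0=0.0424, SE1=0.0377, power above 99%.
- 23 flares: SE0=0.0626, SE1=0.0556, power 86%.
- 14 flares: SE0=0.0802, SE1=0.0713, power 61%.

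The two lower counts come from recruitment to date. Sixteen patients in 265 days (9 October 2025 to 1 July 2026), carried over the 782 days to the closing date of 30 November 2027, give 16/265×782 = 47. Half of 47 is about 23. If the 50% applies to 12 months but only 6 are observed, 47×(1−√0.5) is about 14. These powers ignore within-person correlation and optimism. A separate simulation of a pooled AUC with 50 flares, and within-person marker correlation from 0 to 0.9, still gave power above 99%.

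**4. Testing an apparent AUC.** The cut-off for rejection at 50/50 is 0.6+2.241×0.0566 = 0.727. Data were simulated with N=100, 50 flares and a true AUC of exactly 0.60. A linear score fitted and evaluated in the same patients exceeded the cut-off in about 6% of datasets with 5 predictors and 26% with 10. A logistic version gave 6% with 4 predictors and 37% with 10. The nominal rate is 1.25%. The article gives no predictor count, so these are illustrations.

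**The case against.** A reader might infer that the test is run landmark by landmark on one to three flares, that the AUC is computed on the patients used for fitting, and that both the power and the error rate therefore fail. The documents do not support that much.

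- No section says the test is done at each landmark. The wording on weekly generation fits one model updated weekly as well as separate fits. A pooled AUC would retain the power if the 14-day AUC really is 0.8.
- One to three flares per window is only the 12-month, constant-hazard case. Flares confirmed at three-monthly visits would also cluster, leaving some windows nearly empty and others fuller.
- Nothing says the apparent AUC will be tested. Calling external validation the next step does not exclude bootstrap or cross-validation within this study, and such detail may sit in a full protocol or analysis plan that is not shown.
- The article calls this a development phase producing pilot data.

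All of this stands, and it makes the error-rate point conditional. It does not remove the mismatch: the article itself fixes a 50% event share for the power statement and a 14-day window for the model, and nothing connects the two. The pilot label does not cure this, because a formal null hypothesis, error rate and power are stated.

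**Conclusion.** The stated power is not established for the planned AUC; the documents do not show that it certainly fails. It is correct, and slightly conservative, for a fixed marker with 50% flares (94 to 95% at N=100). At a single 14-day landmark it would be about 5 to 9% with 12 months of follow-up and 10 to 21% with 6 months, assuming 50 flares at constant hazard and the Hanley-McNeil approximation. No follow-up length in the article brings one landmark near 90%. Pooling over landmarks could restore the power, depending on the number of flares observed. The upper-tail error would rise from 1.25% to roughly 6% (5 predictors) or 26 to 37% (10 predictors) only if an uncorrected AUC were tested, which the article neither states nor excludes.

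**What to change.** In Target Recruitment Sample Size:

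1. Name one primary AUC: 14-day horizon, pooled over the weekly landmarks, for example from a stacked landmark model.
2. State that the tested value is optimism-corrected, with resampling by participant that repeats feature selection and the Cox-versus-RSF choice inside each resample.
3. Replace the power sentence with one stated in expected flares. As upper bounds: about 99% at 50 flares, 86% at 23 and 61% at 14, before any loss from within-person correlation or optimism.

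Alternatively, drop the power claim and present N=100 as a pilot size with the expected precision of the AUC.

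The cost is wording and computing time, with no change to visits or data collection. The downside is that the reported AUC and the stated power may look less favourable.
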